#### Sample size and statistical analysis

Approximately 60 participants (MSCs vs control group = 40:20) will be studied. This sample size was chosen to provide a power of 80% and an alpha level of 5% to detect a common odds ratio of 4.75 (across all cut-off points of the mRS), which was the result from the STARTING trial [7]. Possible harmful effects of MSCs will be determined and assumptions underlying the sample size calculation will be adjusted by an interim analysis performed by an independent data and safety monitoring committee (data from 20 eligible participants in the MSC group) [65].

All randomized participants will be included in the endpoint analyses on an intention-to-treat basis. For primary outcome analysis, the categorical shift of mRS at 90 days after treatment will be compared between the MSC and control groups using the Cochran-Mantel-Haenszel shift test and proportional odds logistic regression analysis adjusted for age, sex, stroke mechanisms, and infarct volume on fluid attenuation inversion recovery (FLAIR) imaging 1 day before MSC infusion in the MSC group or 30 days (± 2 days) after randomization in the control group. In this study, the adjusted result is prespecified as the primary outcome analysis. Secondary and exploratory analyses will be performed according to standard statistical methods as appropriate.

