**Figure 2 F2:**
[figure not shown]
**Overall study flow of the 'STem cell Application Researches and Trials In NeuroloGy-2’ (STARTING-2) study.** *Indicates 1 day before mesenchymal stem cell (MSC) infusion in the MSC group vs 30 days (± 2 days) after randomization in the control group.

**Table 2 T2:** Inclusion and exclusion criteria

**No.**	**Criteria type**
Inclusion	
1	Men or women (women must be of non-child-bearing potential), age 30 to 75 years
2	Stroke observed within 90 days of the onset of symptoms
3	Radiological:
	Relevant lesions within the MCA territory as assessed using DWI.
	Maximum diameter of the stroke region in any dimension ≥15 mm
	Damage not involving more than a half of the ipsilateral subventricular zone^a^
4	Clinical (National Institutes of Health Stroke Scale (NIHSS)):
	a. Moderate to severe persistent neurologic deficit (NIHSS of 6 to 21 inclusive)
	b. New onset of extremity paresis on the affected side, defined as a score of 2 to 4 on the NIHSS motor arm (item 5) or leg (item 6) question.
	c. Alert or drowsy but easily arousable as defined by score of 0 to 1 on the NIHSS level of consciousness question (item 1A).
	d. 'Slow recovery’ defined as change in NIHSS ≤1 point/3 days
5	Willingness:
	a. Reasonable likelihood of receiving standard physical, occupational and speech rehabilitation therapy as indicated for post-stroke deficits
	b. Able to participate in the evaluation process to the point of accurate assessment
	c. Willing and able to comply with scheduled visits, lifestyle guidelines, treatment plan, laboratory tests, and other study procedures
	d. Evidence of a personally signed and dated informed consent document
6	Use of antiplatelet, anticoagulant and/or antithrombotic agents is acceptable
Exclusion	
1	Presence of significant disability prior to the current stroke, defined as pre-stroke modified Rankin score of 2 or more
2	Stroke that is either:
	a. Lacunar infarction
	b. Hematologic cause of stroke
	c. Recurrent or progressive stroke within 1 week at the time of screening
3	Hematologic disorders or bone marrow suppression
4	Severe medical illness defined as:
	a. Severe heart failure
	b. Severe febrile illness
	c. Hepatic or renal dysfunction
	d. Active cancer
	e. Any evidence of chronic comorbid condition or unstable acute systemic illnesses which, in the investigator’s opinion, could shorten survival or limit ability to complete the study
5	Presence of HIV, HBV, HCV, or syphilis on admission blood tests

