6	Presence of active depression not adequately controlled that interferes with major activities of daily living immediately prior to the current stroke
7	Presence of dementia prior to the current stroke that is likely to confound clinical evaluation
8	Lactating women or pregnant women as determined by positive urine hCG test
9	Considered unwilling or unable to comply with the procedures and study visit schedule outlined in the protocol
10	Unwilling to undergo bone marrow aspiration

^a^We will measure the degree of involvement of the ipsilateral subventricular zone on the initial diffusion-weighted image at two axial levels; (a) the upper thalamus and head of caudate nucleus and (b) the corona radiate (7-mm upper level).

*DWI* diffusion-weighted image, *HBV* hepatitis B virus, *HCV* hepatitis C virus, *hCG* human chorionic gonadotropin, *MCA* middle cerebral artery.

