#### Randomization and outcomes

Randomization will be in a 2:1 ratio of MSC-treatment to control patients using computer-generated random-permuted blocks with blocks of six subjects. The 2:1 ratio was selected to obtain a sufficient number of participants for explorative analysis in the MSC group. For the primary outcome analysis, the categorical shift in mRS at 90 days after treatment will be determined as 0 to 5 mRS levels. Deaths (a mRS score of 6) will be included in the category of worst outcome (a mRS score of 5). Secondary and exploratory outcomes are shown in Table 3.

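### The primary model adjusts for an infarct volume measured after randomisation on arm-specific time anchors, which conflicts with the declared intention-to-treat set unless values are supplied for unscanned patients

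*Protocol article*

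**What the plan says.** The article's section on randomization and outcomes defines the primary endpoint: "the categorical shift in mRS at 90 days after treatment will be determined as 0 to 5 mRS levels", with deaths placed in level 5.

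The section on sample size and statistical analysis names two methods for it, a Cochran-Mantel-Haenszel shift test and a proportional odds regression. The regression adjusts for age, sex, stroke mechanism and FLAIR infarct volume. The volume comes from "imaging 1 day before MSC infusion in the MSC group or 30 days (± 2 days) after randomization in the control group". The captions of Figures 2 and 3 repeat that pair of anchors: "Indicates 1 day before mesenchymal stem cell (MSC) infusion in the MSC group vs 30 days (± 2 days) after randomization in the control group". It is therefore a design feature and not a slip.

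The same section fixes which result counts: "In this study, the adjusted result is prespecified as the primary outcome analysis". It also fixes the analysis set: "All randomized participants will be included in the endpoint analyses on an intention-to-treat basis".

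Table 2 shows that earlier imaging exists. Lesion location is assessed on DWI, and footnote a measures subventricular involvement "on the initial diffusion-weighted image at two axial levels".

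**The concern.** A covariate in the primary model of a randomised trial should be fixed before allocation and defined in the same way in both arms. This one is neither, and two problems follow.

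- **Selection.** In the MSC arm the scan is dated backwards from an infusion that some patients may never receive. For them the covariate has no definition. Controls need only remain in the study to about day 28. If unscanned patients fall out of the fit, the reasons for falling out differ by arm, and randomisation no longer protects the comparison.
- **Timing.** Lesion volume on FLAIR may change over the weeks after a stroke. If the anchors fall at different times after randomisation, that change appears as an arm difference in the covariate, and the model corrects the treatment effect for it.

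With about 60 patients, a few exclusions or a modest systematic shift can move the result on which the trial will be judged.

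**Working it through.** **1. The two arms side by side (section on preparation and transplantation of MSCs, Table 2, figure captions).**

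| | MSC arm | Control arm |
|---|---|---|
| Before randomisation | Initial DWI | Initial DWI |
| After randomisation, before the FLAIR scan | Serum drawn at once; marrow aspirated within 1 week; culture expansion to the target dose; viability, contamination and marker checks | None of these |
| FLAIR anchor | Infusion minus 1 day; no infusion day in the text or captions | Day 30 ± 2 |
| No value when | Never infused, for any reason | Lost before about day 28 (30 − 2) |

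The images of Figures 2 and 3 were not available for this check.

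**2. The plan's own figure.** The section's only figure is the sample size: about 60 (40:20) for 80% power, alpha 5% and a common odds ratio of 4.75. Whitehead's formula, with A = 2 and a two-sided test, is

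N = 3(A+1)²(z₀.₉₇₅ + z₀.₈)² / [A (ln OR)² (1 − Σp̄³)] = 27 × (1.960 + 0.842)² / [2 × (ln 4.75)² × (1 − Σp̄³)] = 43.64 / (1 − Σp̄³).

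N = 60 needs 1 − Σp̄³ = 43.64/60 = 0.727. The article gives no control mRS distribution. Four plausible ones give N of 46 to 50, and one with 80% of controls at mRS 4 gives 65. So 60 is neither confirmed nor refuted. The covariate does not enter this calculation.

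**3. Selection, illustrated.** All inputs are assumptions except 40:20. There is no true effect, and control mRS 0 to 5 is 1/4/10/20/45/20%. Lost patients are drawn with probability proportional to exp(−latent outcome), so poorer outcomes are lost more often. The test is a complete-case, unadjusted score test for proportional odds. Ranges span repeated runs of up to 15,000 trials per scenario.

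| MSC lost + controls lost | Odds ratio | Two-sided type I error |
|---|---|---|
| 2 + 0 | 1.11–1.13 | 5.9–6.2% |
| 4 + 0 | 1.25–1.26 | 7.7–8.0% |
| 6 + 0 | 1.40–1.42 | 10.7–11.4% |
| 4 + 1 | 1.11 | 6.4% |
| 2 + 1, 4 + 2, 6 + 3 | 1.00–1.01 | 6.3–6.8% |
| Loss unrelated to outcome | – | about 5% |

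In the MSC-only rows the excess is almost all in favour of MSC: 4.5%, 6.9% and 10.6% in one run, against a nominal 2.5%. With proportionate losses it splits roughly evenly between directions.

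Hand check of the 4 + 0 row: Σp³ = 0.108, so V = [36 × 20 × 56 / (3 × 57²)] × 0.892 = 3.69 and SE = 1/√3.69 = 0.521. A bias of ln 1.25 = 0.223 is 0.43 SE. The rejection rate is then 1 − Φ(1.96 − 0.43) + Φ(−1.96 − 0.43) ≈ 6.3% + 0.8% = 7.1%, close to the simulated value.

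**4. Selection and timing with the covariate in the model.** A second simulation (1,500 trials per scenario, 40:20, no effect) fitted a proportional odds model containing the volume. It assumed log-odds of 1 per SD for volume and for unmeasured frailty, with non-infusion dependent on frailty.

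| Scenario | Median odds ratio | Two-sided type I error |
|---|---|---|
| Volume taken before randomisation, all 60 in the model | 1.02 | 5.2% |
| 9% of MSC arm not infused | 1.06 | 5.1% |
| 18% not infused | 1.22 | 8.3% |
| Volume reads 0.25 SD higher in MSC arm | 1.25 | 6.8% |
| Volume reads 0.5 SD higher | 1.60 | 14.8% |
| 9% and 0.25 SD | 1.38 | 10.9% |
| 18% and 0.5 SD | 1.88 | 20.5% |

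Simulation error near 5% is √(0.05 × 0.95/1500) = 0.6 points. The timing rows follow a simple rule: bias in the log odds ratio ≈ (log-odds per SD) × (shift in SD). This gives exp(0.25) = 1.28 and exp(0.5) = 1.65, slightly reduced in the simulation because frailty is not in the model. A shift of the opposite sign biases against MSC by the same factor, for example 1/1.25 = 0.80.

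**The case against.** The strongest reply is that this is a delayed pre-treatment baseline. The endpoint is counted from treatment, and the control visit at day 30 may have been chosen to match the expected pre-infusion visit. The article is also a condensed account, and its analysis plan is not shown. Much of this stands, and it rules out four stronger readings.

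- A reader might infer that the primary analysis is not intention-to-treat. The article declares that it is. Patients drop out only under a complete-case fit, which it does not state. A rule for missing covariates may exist elsewhere, and its absence here is no fault.
- A reader might infer that the scans fall on different days. Only the anchors are known to differ. If infusion falls near day 31, the scan times coincide.
- A reader might infer adjustment for a mediator of the cell effect. The scan precedes infusion, so the cells cannot have altered it, although marrow aspiration and blood draws have already taken place.
- A reader might infer bias in favour of MSC. That needs excess, outcome-related loss in the MSC arm or a timing shift in one particular direction. Culture or release failure could cause excess loss, but nothing in the article links it to outcome.

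The Cochran-Mantel-Haenszel test, as written, does not carry this covariate, so a comparison free of it is available. It is not the result named as primary.

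What survives is the definition itself. A missing-data rule could restore the number of patients analysed, but it could not make the covariate pre-randomisation or align its anchors.

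**Conclusion.** The point holds in this form: the result named as primary depends on a post-randomisation covariate that is anchored differently by arm and has no value for some randomised patients. That conflicts with the promise to analyse everyone unless values are supplied.

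The size cannot be read from the article. Loss rates, their link to outcome, the prognostic strength of volume and any timing shift are all assumed. The illustrations run from no material effect (loss unrelated to outcome, or infusion close to day 31) to an odds ratio of about 1.4 and 11% error for six MSC-only, outcome-related losses. The extreme combined scenario, 18% not infused with a 0.5 SD shift, is higher still. The MSC-only rows are a worst case for selection and not a forecast. Since the covariate can be replaced cheaply, it should be changed before the analysis.

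**What to change.** In the primary model, replace the FLAIR volume with infarct volume measured on the initial DWI, taken before randomisation and defined identically in both arms. State that only variables fixed before randomisation enter the primary model. Move the pre-infusion/day-30 FLAIR volume to the exploratory imaging analyses.

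The sample size does not change. The costs are two. Volume must be measured on existing DWI, which is now required only for location, diameter and subventricular involvement. An early DWI volume may also predict outcome somewhat less well than the later FLAIR volume, which would give up some precision. The age of the DWI will vary between patients, but not by allocation.

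One related definition needs checking at the same time. The endpoint is counted from treatment, so the full protocol or analysis plan should say when it is assessed in MSC patients who are never infused. Changing the covariate alone does not settle that.

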## Discussion

Preclinical and clinical trials have great potential to improve the therapeutic efficacy and safety of MSCs. In the STARTING-2 trial, we are incorporating ischemic preconditioning using ischemic serum, BBB manipulation, and strict selection of candidates for stem cell therapy to improve the therapeutic effects and safety of MSCs. We anticipate that the study results may provide better evidence for the effectiveness of MSC therapy in patients with ischemic stroke.

## Trial status

Start date: November 2012.

Expected end date: February 2016.

Expected publication date: May 2016.

Status at time of submission of this article: recruitment ongoing.
